A new health care centre is established at Oesterbro in eastern Copenhagen as a result of a local collaboration project between the City of Copenhagen, Bispebjerg University Hospital and general practitioners [17]. The health care centre is planned to be responsible for lifestyle rehabilitation of patients with one or more of four selected chronic conditions – type 2 diabetes, chronic obstructive pulmonary disease, chronic heart failure and older patients with balance problems. A new rehabilitation programme combines empowerment-based education, exercise training and dietary advice on a group-based level as one multi-disciplinary intervention.

The aim of the current study is to compare the metabolic, physiological and psychological effects of this new group-based multi-disciplinary lifestyle rehabilitation programme for T2DM patients in a primary care setting with an individual counselling programme in a diabetes outpatient clinic. We hypothesize that patients participating in the group-based rehabilitation programme including supervised exercise will improve their glycaemic control, self-rated diabetes symptoms and quality of life significantly more in the short and long term than patients receiving conventional individual advice on changes in lifestyle.

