### Outcome measures and data collection

The primary outcome measure is glycosylated haemoglobin (HbA1c). Secondary outcome measures are self-rated quality of life and diabetes symptoms. Explanatory outcome measures include blood pressure, lipid profile, body weight, waist circumference, insulin resistance and beta-cell function estimates, and physical fitness. All outcome measures are collected at baseline and at follow-up visits after 6, 12 and 24 months.

At every visit, biochemical, anthropometrical, physiological and physical values are obtained. The same investigator measures the anthropometrical and the physiological outcomes throughout the study. Physiotherapists at the health care centre and at the outpatient clinic complete the physical tests. The patients fill in two self-administered questionnaires on quality of life and diabetes related symptoms at each visit.

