### Quality of life questionnaires

Short Form Health Survey (SF-36) is a multi-purpose, short-form health survey with 36 questions. It yields an 8-scale profile of functional health and well-being scores as well as psychometrically-based physical and mental health summary measures and a preference-based health utility index. The SF-36 has proven to be useful in surveys of general and specific populations, comparing the relative burden of diseases, and has been used to differentiate the health benefits produced by a wide range of different treatments [37]. A higher score on SF-36 indicates an improvement in Quality of Life.

Diabetes Symptom Checklist – Revised (DSC-R) is a self-report questionnaire of 34 questions grouped into 8 symptom subscales measuring the occurrence and perceived burden of diabetes-related symptoms [38]. It has been described to be valid, reliable and responsive to change and to be the only scale that appears to evaluate physical functioning in T2DM patients in a broad, comprehensive manner [39]. A lower score on DSC-R indicates an improvement in Quality of Life.

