### Sample size considerations and statistical methods

The size of the study population is based on the primary outcome measure HbA1c and is estimated on the basis of the results of two meta-analyses relating to education and exercises in T2DM patients [8,14]. According to power calculation, an absolute difference of 0.7% in HbA1c between the groups (power 0.9, significance level 0.05) may be detected with 80 patients in each group. This calculation is based on a standard deviation of the HbA1c-value of 1.3 from larger population studies [40].

Neither patients nor study personnel are blinded to treatment assignment. The study statistician carrying out the data analysis on the primary and secondary outcomes will be blinded and will not have any contact with the patients.

Descriptive statistics (means ± SD, or median and interquartile ranges, as appropriate) will be used to describe the study sample with regards to baseline characteristics. The analysis will be performed according to the intention-to-treat principles using the statistical software SAS 9.1. Comparisons of primary and secondary outcomes between the two groups will be analyzed by values after the intervention at the 6 months follow-up visit, and 12 and 24 months after baseline, using appropriate parametric tests for variables fulfilling the normal distribution criteria or appropriate non-parametric tests for variables not fulfilling the normal distribution criteria. Sensitivity analyses will be carried out with adjustment for possible confounders. When relevant the change in outcomes from baseline to 6, 12 and 24 months follow-up will be assessed. The proportion of patients reaching the recommended goals for glycated haemoglobin, blood pressure and lipids will be compared in a sub-analysis. Statistical significance is set at P < 0.05.

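### HbA1c is compared at three visits under one 0.05 rule, with no visit or combination of visits named as the confirmatory test

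*Protocol article*

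**What the plan says.** All statements are in the protocol article.

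- **Primary outcome** (Outcome measures and data collection): "The primary outcome measure is glycosylated haemoglobin (HbA1c"); no visit is attached. The same section adds: "All outcome measures are collected at baseline and at follow-up visits after 6, 12 and 24 months".
- **Analysis** (Sample size considerations and statistical methods): the group comparisons of primary and secondary outcomes "will be analyzed by values after the intervention at the 6 months follow-up visit, and 12 and 24 months after baseline". The three visits are not ranked. A second form of the endpoint is also kept open: "When relevant the change in outcomes from baseline to 6, 12 and 24 months follow-up will be assessed".
- **Level** (same section): "Statistical significance is set at P < 0.05".
- **Sample size** (same section): "an absolute difference of 0.7% in HbA1c between the groups (power 0.9, significance level 0.05") is said to be detectable with 80 patients per group, using an SD of 1.3 for the HbA1c value. No visit is named. The abstract gives 180 as the number to be randomised.
- **Hypothesis** (Background): the intervention group will improve "significantly more in the short and long term than patients receiving conventional individual advice on changes in lifestyle". The Discussion repeats the short- and long-term wording for glycaemic outcomes.

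**The concern.** The plan has three primary comparisons, one significance level and a sample size worked out for one test. It gives no rule that turns three results into one conclusion. Suppose HbA1c differs at 6 months and not at 24. One reader could call the trial positive because a primary comparison fell below 0.05. Another could call it negative because the hypothesis covers the long term as well. The document does not settle this, so the choice could be made after the results are known.

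The readings carry different error rates. Counting any visit raises the false-positive risk above 0.05. Requiring every visit keeps that risk below 0.05 but lowers power below the single-visit figure. The article says the results may help providers choose between programmes, so the rule for success should be fixed in advance.

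**Working it through.** **Inputs.** Difference 0.7, SD 1.3, 80 per group, level 0.05 and power 0.9, from the sample-size paragraph; 180 randomised, from the abstract (90 per group if split equally); three visits. The article does not state sidedness, and two-sided tests are assumed. It gives no between-visit correlation, so a common value from 0 to 0.9 is assumed and the whole range is shown.

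**1. The plan's own figure.** For two means with normal quantiles:

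n per group = 2 × [SD × (z₀.₉₇₅ + z₀.₉₀) / difference]² = 2 × [1.3 × (1.960 + 1.282) / 0.7]² = 72.5, so 73. The exact t-test needs 74.

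The stated 80 is therefore above what its inputs require, by an unexplained margin in the safe direction.

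**2. Power of one visit taken alone.**

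- 80 per group: standard error = 1.3 × √(2/80) = 0.2055; 0.7 / 0.2055 = 3.41; power = Φ(3.41 − 1.96) = 0.926 (t-test 0.923).
- 90 per group: standard error = 1.3 × √(2/90) = 0.1938; 0.7 / 0.1938 = 3.61; power = Φ(3.61 − 1.96) = 0.951.

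The SD is that of the value, not of the change, so the calculation matches the planned comparison of values at a visit.

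**3. Three visits.** With independent tests and no true effect, P(at least one false positive) = 1 − 0.95³ = 0.143. With independent tests and a 0.7 difference at each visit, P(all three significant) = 0.926³ = 0.794 at 80 per group and 0.951³ = 0.859 at 90. For correlated visits, three equicorrelated normal statistics were simulated (1,000,000 draws for each correlation):

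| Correlation | Any-visit false positive | All-visits power, 80 per group | All-visits power, 90 per group |
|---|---|---|---|
| 0 | 0.143 | 0.79 | 0.86 |
| 0.3 | 0.136 | 0.81 | 0.87 |
| 0.5 | 0.125 | 0.83 | 0.88 |
| 0.7 | 0.109 | 0.85 | 0.90 |
| 0.8 | 0.098 | 0.87 | 0.91 |
| 0.9 | 0.084 | 0.89 | 0.92 |

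The any-visit risk exceeds 0.05 in every row. All-visits power at 80 per group stays below 0.9 in every row. With 90 per group analysed it runs from 0.86 to 0.92, but that assumes no loss to follow-up over 24 months.

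**4. What each decision rule costs at 80 per group.**

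| Rule | False-positive risk | Power |
|---|---|---|
| One pre-named visit at 0.05 | 0.05 | 0.926 |
| Any of three visits, each at 0.05 | 0.084 to 0.143 | 0.96 to above 0.99 |
| All three visits, each at 0.05 | below 0.05 | 0.79 to 0.89 |
| Each visit at 0.05/3 | at most 0.05 overall | 0.844 at a given visit |

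The last rule would need 94 per group for 0.9 power at a given visit. Only the first gives both the 0.05 level and at least the 0.9 power that the sample-size paragraph states.

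**The case against.** **The stated level and power do describe a test.** Each visit's comparison of HbA1c values has a level of 0.05 and more than 0.9 power on the stated inputs. This stands. A reader might infer that the two figures belong to no defined test, and the document does not support that. The gap is narrower: none of these tests is designated as the one that decides.

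**The significance sentence is a general convention, and multiplicity handling can be left to a fuller document.** This stands in part. The sentence does not rule out an adjustment, and a missing adjustment method alone would be no finding in a condensed article. But the article itself fixes three unranked comparisons of the primary outcome, one level, and a sample size for one comparison. Which of them is primary belongs with the definition of the primary outcome.

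**The hypothesis is conjunctive.** It says short and long term, and nowhere that one visit is enough. This is fair, so the 8% to 14% is conditional on an any-visit claim and is not a property of the plan as such. The conjunctive reading does not rescue the power statement at 80 per group, however. It also does not say whether 12 months is included.

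**Secondary outcomes.** A reader might infer a large family of secondary tests, because the quality-of-life section says of the SF-36: "It yields an 8-scale profile of functional health and well-being scores as well as psychometrically-based physical and mental health summary measures", and lists 8 DSC-R subscales. That section describes what the instruments produce. No statement commits the trial to testing every scale at every visit, so a count of such tests, or a claim that chance findings are likely, is not supported.

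**Conclusion.** The concern holds in this limited form: the primary outcome has three unranked group comparisons and no confirmatory one. The 8% to 14% false-positive range applies if any visit counts. The all-visits power of 0.79 to 0.89 at 80 per group (0.86 to 0.92 with all 180 analysed) applies if every visit must be positive. These ranges rest on two-sided tests, an assumed equal correlation of 0 to 0.9 between visits and, for power, a 0.7 difference at all three visits.

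This is not evidence of an underpowered trial. For a single named visit, 73 to 74 per group are enough and 80 give about 0.93. The point should be fixed. It is not severe enough to invalidate the design, because each per-visit comparison is sound on its own inputs.

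**What to change.** Name one HbA1c comparison as primary, giving both the visit and the form. One option is the value at 6 months, the first visit the article describes as following the intervention; the value form matches the SD used for the sample size. State that the 0.7 difference, 0.05 level and 0.9 power refer to that comparison, and that the test is two-sided if that is intended.

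Make the other two visits secondary. Either test them in a fixed sequence at 0.05, each only if the one before is significant, or report them with confidence intervals and no confirmatory claim. If the investigators regard long-term benefit as the main question, a later visit can be the primary one instead; what matters is that it is named before the results are known.

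The change is to wording in the protocol or analysis plan, with no extra patients or visits. The downside is that a favourable result at another visit cannot be claimed as confirmatory if the primary visit fails.

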### Ethics

The study will be conducted according to the principles of the Helsinki declaration. The Danish National Committee on Biomedical Research Ethics and the Danish Data Protection Agency have approved the study protocol.

## Discussion

This prospective, controlled and randomized open label study tests the hypothesis that a new multi-disciplinary group-based lifestyle intervention programme for T2DM patients in a primary health care setting results in better short- and long-term glycaemic outcomes than the traditional best practice for individual lifestyle counselling in a diabetes outpatient clinic setting. The major difference between the two interventions is that the new rehabilitation programme includes a supervised exercise programme, whereas the control group receives advice regarding physical activity. The content and the principles of empowering patients are the same in the two interventions, but the education programme in the health care centre is group-based.

The evidence of the beneficial effects of exercise on diabetes symptoms, physical fitness and quality of life in T2DM is strong [41], and previous group-based non-pharmacological lifestyle studies show improvement in glycaemic control and weight loss compared to individual counselling [9]. Most lifestyle intervention studies have been focused mainly on education, including advice on physical activity and diet, or on exercise training and/or diet. Only a few randomized controlled trials have investigated interventions incorporating several elements of non-pharmacological treatment of T2DM including patient education, supervised exercise and dietary advice on a group-based level [42-45]. However, the number of patients, follow-up time and effects on glycaemic control were very heterogeneous in these studies. It is very important in T2DM management programmes to find ways to increase the impact of non-pharmacological treatment in T2DM patients. Our study may add further evidence to this.

The lifestyle rehabilitation programme is multi-disciplinary including group-based education, dietary advice and exercise, and it is not possible to extract the individual effects of each component. The interventions are non-pharmacological, but the patients are urged to continue their medication throughout the study since the clinical effects of a multi-pharmacological treatment on late diabetic complications are highly significant [46]. Decisions on changes in medication are left to the discretion of the patients' physicians, who are not part of this study.

Disease management programmes tailored to the Danish health care system are currently developed for T2DM and other chronic conditions. Provision of rehabilitation programmes for T2DM patients in a community-based setting, and health care centres, are a possible future part of the organization of prevention and chronic care in primary care, and it is therefore essential to provide evidence for the patient-related effects. The evidence generated from The Copenhagen Type 2 Diabetes Rehabilitation Project may be helpful in the decision making of providers to choose the most suitable lifestyle programme for their T2DM patients.
